# The effects of yoga versus stretching and resistance training exercises on psychological distress for people with mild-to-moderate Parkinson’s disease: study prxotocol for a randomized controlled trial

**DOI:** 10.1186/s13063-017-2223-x

**Published:** 2017-11-02

**Keywords:** Parkinson’s disease, CAM, Mind-body intervention, Yoga, Mindfulness, Exercise, Anxiety, Depression, Randomized controlled trial, Study protocol

## Abstract

**Background:**

Psychological distress is prevalent among people with Parkinson’s disease (PD) and aggravates their motor symptoms, thereby leading to increased disability, high healthcare costs, and poor health-related quality of life (HRQoL). The under-recognition and adverse effects of the pharmacological management of anxiety and depression among the PD population are considerable. Thus, adopting a Complementary and Alternative Management (CAM) approach to address this problem is important. Yoga, one of the most common “mind-body” CAM therapies, can improve the psychological wellbeing of people with chronic illnesses. However, limited research on the effects of yoga in people with PD has been conducted. This study will determine the effects of yoga on the psychological wellbeing of people with mild-to-moderate PD and will compare these effects with those of stretching and resistance training exercises.

**Methods:**

A community-based, single-blind, randomized trial will be conducted. A total of 126 subjects will be recruited and randomly divided into yoga (*n* = 63) or stretching and resistance exercise (*n* = 63) groups. For 8 weeks, the yoga group will receive a weekly 90-min session of yoga, and the control group will receive a weekly 60-min session of stretching and resistance exercises. The primary outcome will be the level of psychological distress measured using the Hospital Anxiety and Depression Scale. The secondary outcomes will include the severity of motor symptoms measured by the Movement Disorders Society – Unified Parkinson’s Disease Scale − Part III Motor Examination; mobility, balance, and fall risk measured by the Timed Up and Go test; spiritual wellbeing measured by the Holistic Wellbeing Scale; and HRQoL measured by the Parkinson’s Disease Questionnaire-8. Assessment will be conducted at baseline, 8th, and 20th weeks of follow-ups.

**Discussion:**

This study will be the first randomized trial to compare the effect of yoga versus stretching and resistance training exercises in a PD population. Results will contribute to the value of yoga as a therapeutic option for managing psychological distress in PD patients. Multiple outcomes including psychological, physiological, and spiritual and HRQoL will also be measured to elucidate the potential mechanisms of yoga. The effect of yoga on people with chronic illnesses will further be elucidated. This information should contribute to future research, practice, and policy related to PD management.

**Trial registration:**

WHO Primary Registry – Chinese Clinical Trials Registry (ChiCTR): CUHK_CCRB00522 Registered on 8 October 2016; date of approval 19 August 2016.

**Electronic supplementary material:**

The online version of this article (doi:10.1186/s13063-017-2223-x) contains supplementary material, which is available to authorized users.

## Background

Parkinson’s disease (PD) affects approximately 10 million people worldwide and is the second most common chronic neurodegenerative disease. Based on demographic changes and prolonged life expectancy, the estimated prevalence of PD is expected to double by 2040 [1]. PD is characterized by four cardinal motor symptoms, namely, resting tremor, rigidity, bradykinesia, and postural instability. The management of PD primarily focuses on the pharmacological replacement of dopamine to control motor symptoms. However, nonmotor symptoms, such as anxiety and depression, reportedly have a great impact on health-related quality of life (HRQoL) and are thus gaining increasing attention [2].

Psychological distress, such as anxiety and depressive symptoms, are prevalent among individuals with PD. The incidence of anxiety and depression in this group is 27.6 to 56%, which is much higher than that in people with other chronic illnesses [3–9]. PD-affected individuals with psychological distress are found to be poor in social communication and prone to adopt a sedentary lifestyle, which compromises their daily role functions and self-care capacity, leading to early retirement and low HRQoL [10]. High psychological distress is also associated with increased disability, progression rate of physical symptoms, incidence of relapse, healthcare costs, and caregiver distress, as well as poor treatment compliance [11–13]. The devastating effects of psychological distress impair the functional status and HRQoL of PD patients, which greatly increase their need and cost for care.

Despite the high prevalence and substantial negative consequences of psychological distress in the PD population, this problem is poorly recognized and rarely addressed [6, 14]. The pharmacological management of anxiety and depression is complicated among PD patients; numerous potential drug interactions exist between antidepressants and PD treatments. Serotonergic agents may exacerbate PD symptoms. Bupropion has a potential dopamine agonistic effect benefitting PD symptoms but potentially worsening psychosis, whereas selegiline has antidepressant and anti-PD effects but may interact with levodopa and with other antidepressant agents [15]. Regarding the negative side effects of pharmacological treatments of anxiety and depression in PD patients, adopting a Complementary and Alternative Management (CAM) approach that addresses psychological distress in PD patients is important [16].

The beneficial effects of CAM on reducing anxiety and depressive symptoms have been demonstrated in individuals with chronic illnesses [17, 18]. Among all nonpharmacological CAM strategies, mind-body exercises are some of the most prevalent ones practiced by individuals with PD given their gentle and easy-to-follow nature [19]. A recent systematic review and meta-analysis of mind-body exercises, which include yoga, dancing, and Tai Chi, has revealed their immediate beneficial effects on the motor symptoms, postural instability, and functional mobility of individuals with mild-to-moderate PD [20]. Yoga has the largest beneficial effect on physical outcomes, but related research on psychological wellbeing is limited. To fill this research gap, this study will investigate the effects of yoga on the psychological wellbeing of individuals with PD.

### Conceptual framework

The Theory of Self-transcendence is the conceptual framework underpinning this research [21–23]. The purpose of this theory is to “provide a framework for inquiry and practice regarding promotion of wellbeing in the midst of difficult life situations, particularly where individuals and families face loss or life-limiting illness” (p.1) [23]. Self-transcendence is an underlying process that explains why people can attain wellbeing while confronting vulnerable conditions; it is theorized as a developmental capacity of a person that naturally emerges when a person encounters vulnerable health experiences. Self-transcendence involves the following four domains: (1) intrapersonal, i.e., how a person views situations that they are facing, (2) interpersonal, i.e., how people interact with others and the environment, (3) temporal, i.e., the capacity to integrate past experiences with outlook in life to obtain a meaningful view of the present situation, and (4) transpersonal, i.e., the capacity to connect with dimensions beyond the typically discernible world, also known as “spiritual consciousness.” How a person responds to difficult life situations, positively or negatively, affects the developmental process of a transcendent sense of self. If positively, people can “go beyond themselves” and self-transcend to attain a state of physical, psychosocial, spiritual wellbeing.

Yoga, which is known as “mindfulness in motion,” is a form of mind-body exercise promoting wellbeing of the body, mind, and spirit. Throughout the mindfulness practice of a sequence of poses (*asana*), breathing exercises (*pranayama*), and meditation (*dhyana*), the awareness and attention to body, mind, and the present moment is raised and sustained. The noncompetitive nature of yoga differs from many forms of exercises relying upon comparison to others or pushing oneself beyond limits to define progress. The guiding principle of yoga is to foster resilience for accepting adversities in life [24]. Through the regular mindfulness practice of yoga, a person can redefine the experience of pain, disability, or difficulty, thereby promoting one’s acceptance of disability and continual functioning beyond physical restraints and vulnerable conditions. Therefore, a yoga intervention is hypothesized to help a person with PD to explore one’s self-boundaries, redefine their illness experience, and self-transcend to attain a sense of wellbeing even in the vulnerable PD trajectory.

## Methods

### Aim

This study aims to examine the effect of yoga on the psychological wellbeing of individuals with mild-to-moderate PD. The objectives will be as follows: to investigate the effect of a structured mindfulness yoga program on (1) psychological wellbeing, (2) physiological wellbeing, (3) spiritual wellbeing, and (4) HRQoL in individuals with mild-to-moderate PD.

### Hypotheses

We hypothesize that (1) the structured mindfulness yoga program will be effective in improving psychological wellbeing, physiological wellbeing, spiritual wellbeing, and HRQoL in individuals with mild-to-moderate PD and (2) the structured mindfulness yoga program will be superior compared to stretching and resistance training exercise in improving psychological wellbeing, physiological wellbeing, spiritual wellbeing, and HRQoL in individuals with mild-to-moderate PD.

### Design

The study will be a single-blinded randomized controlled trial (RCT). Eligible participants will be randomized into experimental or control groups at 1:1 ratio through a permuted block randomization with a block size of 8 [25]. Figure 1 shows the Consolidated Standards of Reporting Trials (CONSORT) flow diagram, schedule of enrollment, interventions and assessments of the study, Fig. 2 shows the Standard Protocol Items: Recommendations for Interventional Trials (SPIRIT) Figure and Additional file 1 the SPIRIT Checklist utilized in the study.

**Fig. 1 Fig1:**
[figure not shown]
Consolidated Standards of Reporting Trials (CONSORT) flow diagram of the study

**Fig. 2 Fig2:**
[figure not shown]
Standard Protocol Items: Recommendations for Interventional Trials (SPIRIT) Figure. The schedule of enrollment, interventions, and assessments. *T0* baseline, *T1* at completion of intervention, *T2* 3 months following the intervention

### Study population

People with mild-to-moderate idiopathic PD will be recruited through two major sources: (1) two PD support groups and (2) two specialized outpatient clinics.

### Inclusion and exclusion criteria

Inclusion criteria include the following: (1) a clinical diagnosis of idiopathic PD, with a disease severity rating of stage I to III on the Hoehn and Yahr scale, (2) age above 18 years old, (3) ability to stand unaided and walk with or without an assistive device, and (4) participants who can give written consent. Exclusion criteria are the following: (1) participants who are currently receiving treatment for mental disorders or with uncontrolled mood disorders, (2) current participation in any other behavioral or pharmacological trial or instructor-led exercise program, (3) cognitive impairment as indicated by the abbreviated mental test score lower than 6, and (4) other debilitating conditions except PD, e.g., hearing or visual impairment, that can impede full participation in the study.

The inclusion criteria are developed to maximize the enrollment of appropriate participants, while the exclusion criteria are used to screen out patients who: (1) have secondary parkinsonism in which symptoms are caused by certain medications, a different nervous system disorder or another illness, (2) with debilitating medical conditions for which yoga or exercise is contraindicated, which pose a risk to safety, preclude fully informed consent, or hinder compliance with interventions (e.g., dementia), and (3) to minimize the risk of potential bias due to current or recent use of other behavioral or pharmacological interventions.

### Sample size

According to a meta-analysis of the effects of yoga on depression compared with aerobic exercise, a moderate effect size of 0.59 was reported for individuals with elevated levels of depression.

In addition, a moderate-to-large effect size of 0.79 on anxiety was found when comparing yoga with relaxation [26]. To anticipate the effect size of at least 0.59 for our primary outcomes (depression and anxiety) and using the power analysis software Gpower 3.1, 47 subjects per arm give a two-arm RCT 80% power to detect an effect size of at least 0.59 at 5% level of significance. Considering previous RCTs of mind-body interventions among people with PD [20], an attrition rate of 25% is taken into consideration. Therefore, 126 subjects with 63 per arm will be recruited.

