### Limitations

We acknowledge two major limitations of this study. First, participation to the study is on a voluntary basis and limit to the mild-to-moderate stage only. People with PD who experience depressive and anxiety symptoms may be less likely to participate in the study. Also, people who are currently taking psychiatric treatment will be excluded. This may limit the generalizability of the findings to those with significant psychological distress. To ameliorate the effects of participation bias, subject recruitment will be conducted in both support groups and outpatient clinics in different geographical areas to increase access to a wider range of people with PD. Second, the single-blind design may expose the study to risks of bias stemming from performance, attrition, and evaluation, which may overestimate the treatment effects. Strategies for minimizing these risks are discussed previously.

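### The 80% power rests on an effect size from people with elevated depression, while eligibility sets no minimum distress, so the figure is unsupported for the population to be enrolled

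*Protocol article*

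**What the plan says.** Sample size takes its planning effect from this source: "According to a meta-analysis of the effects of yoga on depression compared with aerobic exercise", where "a moderate effect size of 0.59 was reported for individuals with elevated levels of depression". It also cites a second figure: "a moderate-to-large effect size of 0.79 on anxiety was found when comparing yoga with relaxation". The first figure is then carried to both outcomes, "To anticipate the effect size of at least 0.59 for our primary outcomes (depression and anxiety", and gives the power statement: "47 subjects per arm give a two-arm RCT 80% power to detect an effect size of at least 0.59 at 5% level of significance". Inflation for 25% attrition gives 63 per arm, 126 in all.

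Inclusion and exclusion criteria list four entry conditions: diagnosis with Hoehn and Yahr stage, age, mobility and consent. None sets a depression, anxiety or HADS score. The first exclusion removes "participants who are currently receiving treatment for mental disorders or with uncontrolled mood disorders".

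Four other sections bear on the mix of participants:
- Background, as a percentage of people with PD: "The incidence of anxiety and depression in this group is 27.6 to 56".
- Primary outcome gives HADS cutoffs (8 or more on a subscale, 15 or more in total) but does not use them for entry.
- Data analysis plans a subgroup analysis by whether psychological distress is present, so participants without it are expected.
- Limitations: "People with PD who experience depressive and anxiety symptoms may be less likely to participate in the study". This is discussed only as a limit on generalizability; effect size and power are not revisited.

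**The concern.** The planning effect belongs to a population that the trial neither requires nor enriches for, and that it partly excludes. HADS cannot fall below zero, so participants who start low have less room to improve, and an average over a mixed sample is plausibly smaller than an average over people with raised symptoms. The attrition allowance does not help, because it replaces lost participants and does nothing about a diluted effect.

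What is at stake is the interpretation of a null result. If readers take the trial as having 80% power for its own population, a non-significant HADS comparison could be read as evidence that yoga adds nothing over exercise, when the design may simply have had less power than stated.

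**Working it through.** **Inputs from the article.** d = 0.59, two-sided alpha 0.05, 1:1 allocation, 47 evaluable per arm, 25% attrition; 27.6% to 56% of people with PD affected by anxiety or depression.

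**Step 1: the plan's own figure.** Two-sample t-test (noncentral t, noncentrality d × √(n/2), df 2n − 2). For d = 0.59 and 80% power, n = 46.08, rounded up to 47 per arm; power at 47 is 80.8%. Inflation: 47 / (1 − 0.25) = 62.7, rounded up to 63 per arm and 126 in total. All reproduce. The smallest effect with 80% power at 47 per arm is 0.584, so the plan has almost no margin below 0.59.

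**Step 2: sensitivity to d.** The article gives no effect for PD patients unselected for distress, so the smaller values are assumptions. Same test, 47 per arm:

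| Assumed d | Power |
|---|---|
| 0.59 | 80.8% |
| 0.50 | 66.9% |
| 0.40 | 48.4% |
| 0.30 | 30.2% |

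**Step 3: a mixed sample.** Assume d = 0.59 in a distressed share p, d0 in the rest, and a common SD. Average d = p × 0.59 + (1 − p) × d0. The Background range supplies p, which is itself an assumption about this sample.

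| d0 in the rest | p = 27.6%: average d, power | p = 56%: average d, power |
|---|---|---|
| 0.3 | 0.380, 44.6% | 0.462, 60.2% |
| 0.2 | 0.308, 31.4% | 0.418, 51.9% |
| 0 (extreme) | 0.163, 12.2% | 0.330, 35.4% |

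Example, first row: 0.276 × 0.59 + 0.724 × 0.3 = 0.163 + 0.217 = 0.380.

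**Step 4: credit for baseline adjustment.** With baseline HADS as a covariate and baseline-to-follow-up correlation r, the residual SD shrinks by √(1 − r²), so the effective d is d / √(1 − r²). The article gives no r. For the d0 = 0.3 row:
- r = 0.6: divisor √0.64 = 0.8; effective d 0.475 and 0.578; power 62.5% and 79.2%.
- r = 0.4: divisor √0.84 = 0.917; effective d 0.415 and 0.505; power 51.2% and 67.7%.

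Adjustment recovers much of the loss in this row. None of the four values reaches 80%, although the best comes close.

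**The case against.** The power sentence is conditional as written: it claims 80% for detecting an effect of 0.59 or more, which is true in any population. Only the choice of 0.59 can be challenged. That stands, and the point is confined to that choice.

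The Pilot study used the same eligibility criteria in ten people and reports a HADS change of −4.7 ± 4.16. Since HADS cannot go below zero, their mean baseline was at least 4.7, and people enrolled under these criteria did improve. This counts against saying that such participants have no room to improve. It does not support 0.59, because the pilot was small and uncontrolled, and a before-after change says nothing about the difference from an exercise arm.

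The dilution figures are fragile. The Background percentage describes PD generally; it is neither the share of this sample above a HADS cutoff nor the source meta-analysis's definition of elevated depression. Zero effect in everyone else is an extreme case. An unadjusted t-test also gives no credit for baseline data, although Data analysis plans a repeated-measures GEE that includes baseline. For these reasons 12% to 35% should not be read as the expected power.

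A reader might also infer that exclusion removes most of the distressed. No figure supports that. Background says that distress in PD is poorly recognised and seldom addressed, so excluding people under treatment may remove few, and Limitations says only that distressed people may be less likely to join.

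The anxiety figure of 0.79 does not rescue the plan, because it is against relaxation and not exercise. Removing it would change nothing either, because the sample size rests on 0.59.

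**Conclusion.** The point holds in a limited form. The calculation is right, but 0.59 is carried without justification from people with elevated depression to a sample with no distress threshold, and for anxiety as well as depression. The stated 80% is therefore unsupported for the enrolled population, and a smaller average effect is plausible.

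A reader might go further and conclude that the effect will fall below 0.59, that the stated power is false, or that a null result is likely. The article does not support these conclusions, because it contains no between-group effect for PD patients unselected for distress.

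The size of the problem can only be bracketed. Power at 47 per arm is about 67% to 30% for d from 0.50 to 0.30. It is about 45% to 60% if the distressed share is 27.6% to 56% and the rest gain 0.3, rising to 62.5% to 79% with baseline adjustment at r = 0.6. The smaller effects, the share of this sample that is distressed, the effect in the rest, the common SD and r are all assumptions.

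**What to change.** 1. In Sample size, state that the 80% with 47 evaluable per arm holds only if the whole sample responds like the elevated-depression source population. Add a sensitivity range labelled as assumption, such as the values in the working.
2. In Data analysis, use baseline HADS as a covariate with T1 and T2 as the outcomes, or keep T0 in the GEE and constrain the baseline means of the two arms to be equal. Do one or the other, so that baseline does not enter the model twice.
3. Replace the distress-present subgroup with an interaction between arm and continuous baseline HADS. Report it as exploratory, because with about 94 evaluable participants (2 × 47) its power is low.

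The cost is a less favourable stated power and a little more analysis work. No extra patients are needed and eligibility does not change. These changes make the power claim honest and the analysis more efficient; they do not guarantee 80% power if the true effect is well below 0.59.

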### Outcomes

#### Primary outcome

Psychological wellbeing in terms of anxiety and depression will be measured by the Hospital Anxiety and Depression Scale (HADS) [41, 42]. This scale has been suggested for use in the PD population as somatic symptoms that may potentially overlap parkinsonian manifestations are not assessed in this scale [43, 44]. The HADS consists of two subscales, namely, anxiety and depressive symptoms. Each subscale consists of seven items, and each item is rated by a four-point scale (range: 0–3). Levels of symptoms of anxiety and depression are considered clinically relevant at a cutoff value of ≥ 8 on each subscale and ≥ 15 for the full scale. The Chinese version of the HADS has demonstrated satisfactory validity and reliability with a Cronbach’s alpha of 0.86 for the overall scale, 0.82 for the depression subscale and 0.77 for the anxiety subscale [41, 42].

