### Data collection

The principal investigator will screen the eligibility of potential participants. For these eligible individuals, an Information Sheet of the study will be provided, and written informed consent will be sought. Information related to demographics and health background will then be collected (Appendix 3). All primary and secondary outcomes will be measured at baseline (T0), 2 months (T1; completion of intervention), and 3 months following the completion of the intervention (T2). All assessment will be conducted during the “on” state of medications to minimize motor fluctuations among participants. Participants will be instructed to follow their normal medication schedule and physical activity and not to start any new, instructor-led exercise program throughout the study period.

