### Data analysis

Descriptive statistics will be used to summarize the demographic, health conditions and clinical outcomes of the participants at three different time points. Normality of the variables will be assessed using the skewness statistic and normal probability plot. The two treatment groups will be examined, at baseline (T0), after the completion of intervention (T1), and 3 months after the completion of intervention (T2), for the changes in psychological distress, motor symptoms, mobility and balance, spiritual wellbeing, and HRQoL among participants. The intention-to-treat principle will be applied in all analyses. The intervention arm will be compared against the control for all primary analysis. Generalized estimating equation (GEE) models, specific with first-order, auto-regressive structure, will be used to assess the differential change of each primary outcome variable (HADS) and secondary outcome variable (MDS-UPDRS-III, TUG, HWS, and PDQ-8), across different time points between the two groups. Completers and noncompleters will be compared to examine any difference in demographic characteristics and health conditions. Prespecified subgroup analyses by gender, level of education, disease staging, and the presence of psychological distress will be conducted. IBM SPSS 22.0 software will be used for statistical analysis. All statistical tests will be two-tailed and statistical significance will be set at 0.05. The final report will follow the CONSORT 2010 guidelines as well as its extension to nonpharmacological interventions.

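### The primary outcome is one HADS score in the abstract but two in the sample-size section, with no primary visit or success rule, so the stated 5% and 80% belong to no identified test

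*Protocol article*

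**What the plan says.** The abstract has a single primary outcome: "The primary outcome will be the level of psychological distress measured using the Hospital Anxiety and Depression Scale". The Sample size section has two. It cites an effect size of 0.59 for depression and 0.79 for anxiety, then plans on "the effect size of at least 0.59 for our primary outcomes (depression and anxiety". From this it derives 47 per arm for 80% power at the 5% level, and 63 per arm (126 in all) after 25% attrition.

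The Primary outcome section does not settle the matter. It says "Psychological wellbeing in terms of anxiety and depression will be measured by the Hospital Anxiety and Depression Scale (HADS", adds that "The HADS consists of two subscales, namely, anxiety and depressive symptoms", and gives cutoffs for each subscale and for the full scale. It does not say which score is tested.

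On timing, the Data collection section says "All primary and secondary outcomes will be measured at baseline (T0), 2 months (T1; completion of intervention), and 3 months following the completion"; the last of these visits is labelled T2. The Data analysis section uses GEE models for the "differential change of each primary outcome variable (HADS) and secondary outcome variable" across time points between the groups, and then states: "All statistical tests will be two-tailed and statistical significance will be set at 0.05". No section names T1 or T2 as primary, or says what combination of results counts as success.

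**The concern.** The second hypothesis is that yoga is superior to stretching and resistance training. A reader should be able to point to the one result that decides it. The article allows the total score or the two subscales, at T1, at T2 or over both.

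The 5% and 80% were worked out for one comparison, and the article does not say which. If the choice among scores and visits stays open until the data are seen, a positive claim could carry more than 5% risk of error. If both subscales must succeed, the chance of success may fall short of 80%.

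**Working it through.** **Inputs from the article.** Effect size 0.59 (depression) and 0.79 (anxiety), planned as at least 0.59 for both; 80% power; two-sided 0.05; 1:1 allocation; 25% attrition; visits T1 and T2.

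**Inputs assumed.** The article gives no correlations. I take 0 to 0.8 between the subscales and 0.4 to 0.7 between the visits.

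**1. The article's own figure.** A two-sample t-test with d = 0.59, two-sided 0.05 and 80% power needs n = 46.1, so 47 per arm; power at 47 is 80.8%. Attrition: 47 / 0.75 = 62.7, so 63 per arm and 126 in total. The arithmetic is right, for one test.

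**2. False-positive rate if any one result suffices, each at 0.05.**
- Two subscales, one visit, independent: 1 - 0.95² = 9.75%. With correlation 0.5 it is 9.1%; with 0.8, 7.8%. Range: about 8-10%.
- Two subscales at T1 and T2 tested separately: 1 - 0.95⁴ = 18.5% if all four are independent. By multivariate-normal simulation it is 17.8% (subscale correlation 0, visit correlation 0.4) down to 12.8% (0.8 and 0.7). Range: about 13-18%.

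**3. Power at 47 per arm** (normal approximation, which gives 81.6% for a single test where the t-test gives 80.8%). The expected test statistic is d × √(47/2): 0.59 × 4.848 = 2.860 and 0.79 × 4.848 = 3.830. Single-test power is Φ(2.860 - 1.960) = 0.816 and Φ(3.830 - 1.960) = 0.969.

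| Success rule (one visit) | Overall error | Power, d = 0.59 on both |
|---|---|---|
| Either subscale, each at 0.05 | about 8-10% | 88-97% for at least one |
| Both subscales, each at 0.05 | at most 5% | 67-75% |
| Bonferroni, each at 0.025 | at most 5% | 71.9% per subscale (t-test); 82-93% for at least one |
| Holm | at most 5% | about 77-79% per subscale; 82-93% for at least one |

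The independent cases can be checked by hand:
- Both: 0.816² = 0.666.
- Either: 0.816 + 0.816 - 0.666 = 0.966.
- Bonferroni, normal approximation: Φ(2.860 - 2.241) = 0.732 per subscale, so 1 - (1 - 0.732)² = 0.928 for at least one.
- Holm, per subscale: 0.732 + (0.816 - 0.732) × 0.732 = 0.793.

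The other end of each range is at subscale correlation 0.8.

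**4. Both required, with the cited effects.** For 0.59 and 0.79, independence gives 0.816 × 0.969 = 0.791. At correlation 0.8 it is 0.813. Range: about 79-81%.

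**5. Size for 80% per subscale at 0.025.** n = 55.9, so 56 per arm; 56 / 0.75 = 74.7, so 75 per arm and 150 in total.

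**The case against.** A reader might infer that neither the 5% nor the 80% holds. The documents do not support that. The two failures need different success rules. If either subscale suffices uncorrected, error rises but power does not fall. If both are required at one visit, power may fall but error stays at or below 5%. For one HADS score at one visit, both figures hold for the assumed effect.

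A reader might also infer four separate primary tests and an error rate about three times the nominal one. That is the least favourable reading. The article does not say that T1 and T2 are tested separately, and one joint group-by-time test per outcome fits the wording as well. The Data analysis section puts only HADS in its parenthesis, which suits a single primary score. The pilot likewise reports a single HADS change.

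The 67-75% sets both effects at the planning floor. With the article's own 0.79 for anxiety, requiring both gives about 80%, so the power loss nearly disappears. All these figures are also for a two-sample comparison, while the planned GEE uses repeated measures and may have different power.

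Finally, a condensed article may leave the multiplicity rule and the exact model contrast to a full protocol or analysis plan. That is fair, and their absence alone would not be a finding. What stands is that the article itself states the number of primary outcomes in two ways, and attaches a one-test calculation to the plural version. A separate plan would have to override one of the published statements.

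**Conclusion.** The concern holds in a conditional form. The abstract and the Sample size section disagree on whether there are one or two primary outcomes, and nothing in the article fixes the visit or the success rule. The sample-size arithmetic is correct for a single comparison that the article does not identify. As written, 5% and 80% are guaranteed together only for one HADS score at one visit.

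Under the other readings the cost falls either on error or on joint power, by the amounts shown above. The 13-18% figure further requires that T1 and T2 be tested separately. The ranges rest on the assumed correlations and on a two-sample approximation to the GEE, but the need to name the deciding test does not depend on either.

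**What to change.** Reconcile the abstract, Sample size, Primary outcome and Data analysis sections by naming one primary test before outcome data are seen by arm. One example is the HADS total at T1, yoga versus control, two-sided 0.05, with the subscales and all T2 contrasts secondary. State that d = 0.59 is an assumption for the total, because the cited effects are for depression and anxiety separately. The 47, 63 and 126 then stay as they are.

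If both subscales are to remain primary, name one visit and one rule, and restate power at 47 per arm for d = 0.59 on both:
- Bonferroni: about 72% per subscale.
- Holm: about 77-79% per subscale, and 82-93% for at least one.
- Both required: about 67-75%.

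The cost is wording only. The price is that subscale and T2 claims become secondary, or that the stated power becomes slightly less favourable. Recruiting more participants arises only if the trial wants 80% per subscale at a split level (150 in total under Bonferroni).
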